## Abstract

**Background:**

The PROFRUVE study is a controlled intervention based on the Theory of Planned Behavior (TPB), which follows those behavioral theories that have proved to be the most effective at changing infant fruit and vegetable (FV) intake pattern. The main purpose of the study is to evaluate the effectiveness of an intervention program in increasing FV consumption in schoolchildren aged 8 to 10 and based on TPB.

**Methods:**

Eligible classrooms within schools from Vitoria-Gasteiz (Basque Country, Spain) will be randomly assigned to the intervention (classrooms *n* = 4; children *n* = 86) or control (classrooms *n* = 4; children *n* = 86) group. The intervention group will receive 14 sessions of 60 min during an academic year (October to June). These sessions, designed by a multidisciplinary team, are based on TPB and are directed at modifying determinants of behavior (attitudes, subjective norms, perceived behavioral control and intention of consumption), and intake of FV itself. Both the process and the evolution of consumption and determinants of behavior will be evaluated (before, during, shortly after and a year after) using validated surveys, 7 day food records, 24 h reminders and questionnaires.

**Discussion:**

This study will provide a valid and useful tool to achieve changes in the consumption of FV at school level. A negative result will be helpful in redefining new strategies in the framework of changing habits in the consumption of FV.

**Trial Registration:**

This study has been retrospectively registered at ClinicalTrials.gov. Identifier: NCT03400891. Data registered: 17/01/2018.

## Background

Developed societies are characterized by their unhealthy eating patterns, which contribute to the high prevalence of overweight and obesity according to WHO. As a consequence it is a massive costly public health matter. The ALADINO 2015 study has shown overweight rates of 23.4% and obesity rates of 18.1% among 6–9 years old Spanish children. The data from the same study relating to the Basque Country indicate a high prevalence: 24.1% overweight among girls and 21.8% among boys, and 8.3% obesity among girls and 14.1% among boys [1]. Our research group analyzed the youth population of Vitoria-Gasteiz, the capital of the Basque Country, located in the north of Spain. These data showed that 22% of the schoolchildren aged 6 to 17 were overweight and 3.2% obese (unpublished data of City Council Nutritional Observatory, 2007).

Bad eating habits are at the head of the most frequent causes of weight problems [2]. Sufficient intake of fruit and vegetable (FV) has direct repercussions on dietary energy intake. It is a key in eating habit which promotes healthy weight because of its low caloric value and its fiber supply in the diet [3, 4]. In addition, increased FV intake has been shown to have a beneficial effect on bone density [5], cardiovascular health [6–8], diabetes [9], cancer [10] and metabolic syndrome [11].

According to the ENALIA Study, among Spanish youngsters under 17 years, only 31.7% use to eat FV daily [12]. The latest study carried out in the Basque Country, showed that children and youngsters aged 4 to 18 usually eat 98.9–114.2 g of fruit per day (boys and girls respectively) and 90.3–86.5 g of vegetables per day (boys and girls) [13]. This is a long way from the recommended 400 g of FV per day [14]. In Vitoria-Gasteiz, only two in ten children and adolescents (aged 6 to 17) consume the recommended three servings of fruit and only one in ten the recommended two servings of vegetables daily. Average intake of fruit was 1.8 servings/day and 0.8 servings/day for vegetables (unpublished data of City Council Nutritional Observatory, 2007). For this reason, promotion of sufficient intake of FV must be a priority objective in the promotion of healthy eating habits.

Taking into account that the habits acquired in childhood tend to remain in adulthood [15] and that food education and healthy lifestyle adequately raised are effective in the infant population, nutrition education seems to be the ideal tool for increasing FV intake [16]. For this purpose the school environment is the perfect scenario for training both healthy eating and lifestyle healthy habits [17, 18]. It is of paramount importance to involve all those engaged in the education of children: parents and teachers [19, 20] and even classmates [21].

However, the food environment has become increasingly complex and just to transfer information on eating and lifestyle habits is not enough to modify them [22, 23]. Other intervention approach is to use behavioral theories to understand and modify food choice behavior [23–25]. One of the most widely used theories backing these types of interventions is the Theory of Planned Behavior (TPB). According to this theory eating behavior and intention of consumption determinants are both personal and environmental. Specifically, the TPB states that attitude, subjective norms and perceived control are determinants that influence both the intention to consume and the action of consuming food [24].

According to the scientific bibliography, the most effective programs that have attempted to modify the pattern of infant feeding in terms of FV have been those that contemplate the determinants of eating behavior [25–27]. In fact, with regard to a meta-analysis that studied the influence of behavioral theory-based interventions on children’s FV intake, the effectiveness of theory-based and non–theory based studies differed significantly. Moreover, the intervention was more effective when it was theory-based than non–theory based, irrespective of the number of theories used for the interventions. Furthermore it was concluded that the quality of the study is more important than the theory itself or the number of theories used [27].

### Hypothesis

An intervention program to increase FV intake in schoolchildren aged 8 to 10 and based on TPB will produce changes in attitude, subjective norms, perceived behavioral control and intention of eating FV, which in turn will modify behavior, thus increasing FV intake.

### Objectives

The main objective of this study is to evaluate the effectiveness of an intervention program based on TPB in increasing FV intake in schoolchildren aged 8 to 10.

Secondary objectives of the study are (i) to evaluate the change in FV intake in the study population after intervention, (ii) to examine the impact of the intervention program on behavioral determinants, (iii) to analyze the association of the behavioral determinants with FV intake, and (iv) to study the relationship between social demographic variables and the effectiveness of the program.

## Methods

### Design

A cluster randomized controlled trial will be carried out over an academic year at school level. Classrooms from different schools and schools themselves will be the clusters of the study. Clustering was chosen because this is the easiest way to implement an intervention program at school level. In this way the phenomenon of contamination between children from the same classrooms is avoided.

Whole classes (a minimum of 26 children per classroom) from different schools will be part of the intervention or control group. The control group allows us to analyze the direct effect of the intervention and to discard an increase of FV intake by seasonality (first measurements will be in October and final ones in June) or other factors. The study was approved by the Ethic Committee of the University of the Basque Country (CEISH/262/2014/[name]) and all parents or legal guardians and school directors and teachers will be sent an informed consent before the study starts. Written informed consents will be sent to parents or legal guardians through the children. After having received consents, the collection of the first data will be carried out followed by the randomized allocation of classrooms.

### Participants

The study will be conducted in schools from the capital of the Basque Country: Vitoria-Gasteiz. The classrooms within schools for this study will be randomly selected from a list given by the City Council of Vitoria-Gasteiz. Contact between the research group and schools will be made by the City Council.

The schools will be chosen to be representative in terms of ethnicity and social economical status. The inclusion criteria for this sample are: all schools from Vitoria-Gasteiz containing enough children aged 8 to 10 per classroom (a minimum of 26 children) and orchard. The exclusion criteria are: special schools and schools that are carrying out some other program related to healthy eating habits promotion in the same period. Having carried out previous nutritional programs will not be considered an exclusion criterion because the majority of schools from Vitoria-Gasteiz have participated in different programs organized by the City Council.

### Sample size

In order to provide a power of 90% to detect an effect size (Cohen’s d) of at least 0.5 servings/day, 172 participants (86 in the intervention group and 86 in the control group) are required. Based in the dropout of similar studies [28–30], the final sample size is increased by 20% to reach 206 children (8 classrooms with a minimum of 26 children per class).

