### Statistical analysis

Descriptive statistics will be carried out to describe baseline characteristics of intervention and control group to assure comparability between groups.

Intra-group and inter-group FV intake differences at T0, T1, T2 and T3, will be analyzed by Student’s *t* test or non-parametric tests (Wilcoxon signed-rank test and Mann–Whitney U test). The same tests will be carried out to study the evolution of determinants of eating behavior (attitude, subjective norms, perceived behavioral control and intention) at different times.

To understand the relationship between determinants of behavior and behavior itself (FV consumption), multiple linear regression and structural equation modeling (SEM) analysis will be done at different times. Covariance of classic relationship of TPB determinants will be proposed. It will allow us to check the validity of the proposed model, as well as the influence of each determinant on the others and its significance. Changing models will be made by using difference on TPB determinants between different times.

Model validity will be established by comparative fit index (CFI), root mean square-error of approximation (RMSEA) and chi square/degrees of freedom (χ2/df). A good model will be determined by high values of CFI (> 0.90), low values of RMSEA (< 0.10) and χ2/df values from 1 to 3 [35, 36].

Multiple linear regression will be used to study the effect of social demographic variables in the effectiveness of the intervention.

Statistical analyses will be made using STATA 14.0, IBM-SPSS 24.0 and AMOS 24.0 statistical software. IC of 95% and significance level of *p* < 0.05 will be assumed.

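### The 90% power for 86 children per arm is an individually randomised figure; it makes no allowance for allocating only 4 classrooms to each arm

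*Protocol article*

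**What the plan says.** All references are to the protocol article.

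- **Design** section: "A cluster randomized controlled trial will be carried out over an academic year at school level". Whole classes go to one arm or the other.
- **Abstract, Methods**: classrooms "will be randomly assigned to the intervention (classrooms *n* = 4; children *n* = 86) or control (classrooms *n* = 4; children *n* = 86) group".
- **Sample size**: the target power is 90%. The effect size is called a Cohen's d but carries a unit, "of at least 0.5 servings/day". From these two inputs the section concludes that "172 participants (86 in the intervention group and 86 in the control group) are required". A separate step then allows for dropout: "the final sample size is increased by 20% to reach 206 children (8 classrooms with a minimum of 26 children per class").
- **Statistical analysis**: "Intra-group and inter-group FV intake differences at T0, T1, T2 and T3, will be analyzed by Student’s *t* test or non-parametric tests", with "significance level of *p* < 0.05 will be assumed". The section names no classroom term.

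No ICC, design effect or number of classrooms enters the derivation of 172.

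**The concern.** Children in one classroom share a teacher, the programme sessions and, by design, peer influence: the class intake poster is meant to work through social pressure. Their intakes are unlikely to be independent. When classrooms are randomised, the precision of the comparison depends on the variation between classrooms and on how many there are, here 8. A power figure that counts children as if each had been randomised separately overstates what the design can do.

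The Discussion section intends to use a negative result to redesign strategies. A reader who trusts 90% will take a non-significant result as fairly strong evidence against an effect of the target size. The design does not support that inference once the classrooms are analysed validly.

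This is not a detail that a condensed article leaves to a fuller document. The published number can be traced to a formula that does not match the published design, and no later document could put a design effect inside 86 per arm.

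**Working it through.** **Inputs from the protocol article.** Power 90%, d = 0.5, significance level 0.05, 86 per arm (Sample size and Statistical analysis sections); 4 classrooms per arm (Abstract); at least 26 children per class (Sample size section).

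**Assumptions.**
- The test is two-sided. The article does not say so, but a one-sided 0.05 needs about 70 per arm and does not reproduce 86.
- d is standardised. The article attaches servings/day to it, and the two agree only if the SD is 1 serving/day.
- The ICC ranges from 0 to 0.10, because the article gives none.

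**Step 1. Reproduce the plan's figure.** A two-sample t test on independent children with d = 0.5, two-sided alpha 0.05 and 90% power needs 85.03 per arm, rounded up to 86, so 172 in total. Power is 90.3% at 86 per arm. The match is exact, and 172 × 1.2 = 206 uses up the stated increase. There is no room for a design effect.

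**Step 2. Put the classrooms in.** With k = 4 classrooms per arm, n analysed children per arm and m = n/k:

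- design effect DE = 1 + (m − 1) × ICC
- noncentrality = d × √(n / (2 × DE))
- degrees of freedom = 2 × (k − 1) = 6, two-sided critical value 2.447

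For n = 86, m = 21.5. At ICC 0, DE = 1 and the noncentrality is 0.5 × √43 = 3.279, so power is 77.9%. At ICC 0.05, DE = 1 + 20.5 × 0.05 = 2.025, the noncentrality is 3.279/√2.025 = 2.304, and power is 49.0%.

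| Assumed ICC | DE (86 per arm) | Power, 6 df, 86 per arm | Power, 6 df, all 26 per class kept (104 per arm) | Power, design effect and normal critical value, 86 per arm | d detectable with 90% power (6 df, 86 per arm) |
|---|---|---|---|---|---|
| 0 | 1.000 | 77.9% | 85.0% | 90.6% | 0.60 |
| 0.01 | 1.205 | 70.3% | 76.6% | 84.8% | 0.66 |
| 0.02 | 1.410 | 63.6% | 69.1% | 78.9% | 0.71 |
| 0.05 | 2.025 | 49.0% | 52.2% | 63.5% | 0.85 |
| 0.10 | 3.050 | 35.3% | 36.8% | 46.7% | 1.04 |

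No column adjusts for covariates. Keeping every child helps little at the higher ICCs, because the number of classrooms is what limits precision.

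**Step 3. What the tests named in the article would do.** If the child-level test ignores classroom, its statistic has variance DE instead of 1. By normal approximation with 86 per arm, type I error is 2 × [1 − Φ(1.96/√DE)]: about 7% at ICC 0.01, 17% at 0.05 and 26% at 0.10. For d = 0.5 the same test rejects about 88.5%, 82.3% and 77.6% of the time. Its rejection rate stays high because it rejects too often under the null as well.

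**The case against.** Three objections deserve weight.

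**A reader might infer that 8 classrooms miss 90% at every ICC, whatever the method.** The article does not support that. At ICC 0 the child-level t test gives 90.3%. A design effect with a normal critical value keeps 90% up to an ICC of about 0.001 with 86 per arm, and up to about 0.009 with 103 to 104 per arm. Failure at every ICC holds only for an unadjusted test on the 6 between-classroom degrees of freedom. That condition belongs in the statement. The shortfall itself does not depend on it: the design-effect method alone gives 63.5% at ICC 0.05.

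**A reader might infer that the trial, analysed as written, has little chance of finding the target effect.** That does not follow either. The tests named in the article ignore classroom, and their main danger is a false positive (step 3). The low power belongs to a valid analysis that the article does not yet name. Even then, 64% to 78% at ICCs up to 0.02 is reduced power rather than little chance. This objection stands, and it is why the power statement and the analysis must be corrected together.

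**Adjusting for baseline intake would recover power.** It would. With an assumed baseline correlation of 0.6 and the variance reduced in proportion at both levels, 6-df power with 86 per arm is about 92% at ICC 0, 82% at 0.02 and 67% at 0.05. But the article neither plans this adjustment for the group comparison nor credits it in the sample size, so it does not rescue the stated 90%.

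**Conclusion.** The concern holds with its conditions stated. The arithmetic behind 172 is right for independent children; the error is to assume independence in a cluster-randomised trial. That 86 per arm contains no clustering allowance is established by exact reproduction and needs no assumed ICC.

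The size of the shortfall does depend on assumptions. For an unadjusted classroom-level test on 6 df at d = 0.5, power is at most about 78% with 86 analysed per arm, or 85% if all 26 children per class are kept. At an assumed ICC of 0.05 it is about 49% or 52%. No single shortfall can be fixed, because the article gives no ICC. The 90% claim should not stand for the design described.

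**What to change.** Keep the 8 classrooms and rewrite the sample-size paragraph:

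1. Remove the 90% claim, or label it as the figure for independently randomised children.
2. State the power at d = 0.5, or the effect detectable with 90% power, for 4 versus 4 classrooms over an ICC range such as 0.01 to 0.10. Use 6 degrees of freedom and say that no covariate adjustment is assumed. With 86 analysed per arm, that is power of about 70% down to 35%, or a detectable effect of about 0.66 up to 1.04 SD.
3. Pair this with a cluster-adjusted between-group analysis in the Statistical analysis section. The restated power describes no planned test otherwise.
4. Say that a non-significant result will be interpreted through the cluster-adjusted confidence interval, not as evidence of no effect.

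The cost is one rewritten paragraph plus the matching change to the analysis text, with no extra recruitment. The downside is a visibly less favourable power statement. Reaching 90% would take more classrooms: at 26 per class and with the same unadjusted classroom-level test, 6 per arm at ICC 0.02, 9 at 0.05 and 13 at 0.10. That is not proposed here for a trial reported as ongoing.

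### The 20% dropout allowance is applied as 172 × 1.2 = 206; if 20% is the expected loss, about 165 children remain, not the 172 required, and the abstract gives 86 per arm as the number assigned

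*Protocol article*

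**What the plan says.** The Sample size section of the protocol article begins "In order to provide a power of 90% to detect an effect size (Cohen’s d) of at least 0.5 servings/day", and for this "172 participants (86 in the intervention group and 86 in the control group) are required". It continues, citing dropout in similar studies, that "the final sample size is increased by 20% to reach 206 children (8 classrooms with a minimum of 26 children per class". It gives no dropout rate other than this 20%.

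The Methods paragraph of the abstract says that classrooms "will be randomly assigned to the intervention (classrooms" and gives, in the bracket that follows, 4 classrooms and 86 children, with the same numbers for control. The Design section says that whole classes of at least 26 children enter the trial.

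**The concern.** An allowance for dropout should leave the required number after the loss. If a fraction *d* is lost, the number to recruit is *n*/(1 − *d*). Multiplying by (1 + *d*) always gives less than this. If the 20% is the loss the plan expects, the 206 does not deliver the 172 that the same section calls required.

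The abstract raises a second question. It attaches 86 children per arm to the act of assignment, whereas the Sample size section uses 86 per arm for the number needed before dropout is allowed for. A reader of the abstract alone would take 172 as the number randomised; a reader of the Sample size section would take 206. This affects how recruitment and attrition are later judged against the plan.

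**Working it through.** **Inputs.** From Sample size: power 90%, Cohen's d 0.5, 172 required (86 per arm), a 20% increase, 206 children, 8 classrooms, minimum 26 per class. From Statistical analysis: "significance level of *p* < 0.05 will be assumed". Sidedness is not stated. Two-sided is assumed because it reproduces the plan's figure; one-sided gives 69–70 per arm and does not.

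**1. The 172.** Normal approximation: n per arm = 2(1.960 + 1.282)²/0.5² = 84.1, rounded up to 85. The exact t-test calculation gives 85.03, rounded up to 86. Then 2 × 86 = 172, which reproduces the plan. This is an individual-level formula with no term for clustering.

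**2. The 206.** 172 × 1.2 = 206.4, stated as 206. The multiplier reproduces the figure. Division does not: 172/(1 − 0.20) = 215.

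**3. What remains after 20% loss.**
- From 206: 206 × 0.80 = 164.8, about 165, which is 7 below 172.
- From 8 × 26 = 208: 208 × 0.80 = 166.4, about 166, which is 6 below 172.
- From 8 × 27 = 216: 216 × 0.80 = 172.8, which meets the requirement.

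**4. The loss that 206 can bear.** 1 − 172/206 = 16.5%. For 208 it is 1 − 172/208 = 17.3%. Because the plan states no rate, the range for 206 is: 10% loss leaves 185, 15% leaves 175, 20% leaves 165.

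**5. Power** (individual-level t-test, two-sided 0.05, d = 0.5). With 86 per arm it is 90.3%. With 82 per arm (164.8/2 = 82.4, rounded down) it is 88.9%. The difference is 1.4 percentage points.

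**6. Whether 215 would secure 90% power in this design.** The documents give no intraclass correlation (ICC), so 0.01, 0.02 and 0.05 are assumed. Completers per class are 164.8/8 = 20.6 from 206 recruited and 172/8 = 21.5 from 215. The design effect is 1 + (m − 1) × ICC, and the effective total is completers divided by it.

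| Assumed ICC | 206 recruited | 215 recruited |
|---|---|---|
| 0.01 | 164.8/1.196 = 137.8 | 172/1.205 = 142.7 |
| 0.02 | 164.8/1.392 = 118.4 | 172/1.410 = 122.0 |
| 0.05 | 164.8/1.980 = 83.2 | 172/2.025 = 84.9 |

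Moving to 215 adds about 2 to 5 effective children, and neither column reaches 172.

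**7. The abstract.** 86/4 = 21.5 children per class, below the stated minimum of 26. Four classes of at least 26 give at least 4 × 26 = 104 per arm; half of 206 is 103.

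**The case against.** The strongest reply is that the plan never states a 20% dropout rate. It states a 20% increase, which it bases on dropout in similar studies, and 206 follows correctly from that. If the cited studies support a loss of 16.5% or less, 206 is enough. This stands as a limit on certainty: a reader might infer that the plan contradicts an explicit dropout figure, and the text does not go that far. Even so, a 20% addition attributed to dropout is most naturally read as 20% expected loss, and the text offers no other rate.

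The second reply is that 26 is a minimum. Whole classes enter, and an average of 27 gives 216, above 215. This also stands: the shortfall applies to the stated target of 206 and to classes at the floor, and the 8-classroom design could meet the corrected figure unchanged.

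A reader might go further and argue from the consent procedure ("all parents or legal guardians and school directors and teachers will be sent an informed consent before the study starts") that 208 pupils leave room for only two refusals, so that power would fall well below 88.9%. The documents do not support this. They give no consent rate, do not say whether the 206 counts pupils enrolled or children with consent, and do not fix classes at exactly 26.

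On the abstract, it may be said that 86 is only shorthand for the analysis target. That is probably how it arose, but the sentence ties the number to random assignment, and the mismatch does not depend on any view of dropout.

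**Conclusion.** The point holds and is minor. If 20% is the expected loss, the stated 206 leaves about 165 children, 7 short of the plan's own 172, and 215 would be needed. The cost is about 1.4 points of individual-level power. The conclusion rests on reading the 20% as a dropout rate and on classes at or near the minimum size; at 16.5% total loss or less there is no shortfall.

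The discrepancy between the abstract and the Sample size section needs neither assumption: 86 per arm cannot be the number assigned when 4 whole classes of at least 26 enter each arm.

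A reader might infer that correcting 206 to 215 would give the trial 90% power. It would not. All the power figures here are individual-level, as is the plan's 172, and the correction hardly changes the effective sample size once clustering is counted.

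**What to change.** - In Sample size, state the expected dropout rate behind the 20%. Then either give 215 (172/0.8) as the target for 20% loss, about 27 per class in 8 classes, or keep 206 and say that it tolerates at most 16.5% total loss.
- Do not describe either change as restoring 90% power for the clustered design.
- In the abstract, give 86 per arm as the completer target and about 103–104 per arm as the number to be randomised (about 108 if 215 is adopted, since 215/2 = 107.5).

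The cost is a few restated figures. Keeping 206 with its tolerated loss needs no added recruitment, and adopting 215 needs none if classes average 27.

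### If the 20% allowance is the expected dropout, multiplying 172 by 1.2 under-covers it: 206 children leave about 165, slightly below the stated requirement (minor correction)

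*Protocol article*

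**What the plan says.** The Sample size section sets the target in two steps. First, for 90% power at an "effect size (Cohen’s d) of at least 0.5 servings/day", it says that "172 participants (86 in the intervention group and 86 in the control group) are required". Second, it adds an allowance, which it bases on dropout seen in comparable studies: "the final sample size is increased by 20% to reach 206 children (8 classrooms with a minimum of 26 children per class". The 20% is given as the size of the increase. The article nowhere states an expected dropout rate as such.

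The minimum of 26 children per class also appears as a design condition (Design: "Whole classes (a minimum of 26 children per classroom") and as a school inclusion criterion (Participants). The Statistical analysis section sets the significance level at 0.05 without saying whether the test is one- or two-sided.

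**The concern.** An increase of 20% and a loss of 20% do not cancel. If a fraction d of the recruited children is lost, the number to recruit is the required number divided by (1 − d). Multiplying by (1 + d) always gives too few. The article attributes its 20% directly to dropout and mentions no other rate, so most readers will take 20% as the loss planned for. On that reading the recruitment target does not deliver the analysed number that the same section calls required. The floor of 26 per class, which matches that target, falls short as well. At stake is whether the stated 172 and the stated 90% power survive the plan's own allowance.

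**Working it through.** **Inputs.** Power 90%, d = 0.5, 86 per arm (172 in total), a 20% increase to 206, and 8 classes of at least 26 (all from Sample size); alpha 0.05 (Statistical analysis). Assumptions: a two-sided test, and 0.5 read as a standardised difference, because no standard deviation is given.

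**Reproducing 172.** A two-sample t test with d = 0.5, two-sided alpha 0.05 and power 0.90 solves at 85.03 per arm. This rounds up to 86 per arm, 172 in total, as stated. The normal approximation gives 85 per arm. A one-sided test would give 69 per arm by that approximation, so two-sided is the reading that fits.

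**Reproducing 206.** 172 × 1.2 = 206.4, reported as 206. The allowance was therefore multiplied.

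**What is left if 20% drop out.**
- From 206: 206 × 0.8 = 164.8, about 165, which is 7 below 172.
- From the class minimum: 8 × 26 = 208, and 208 × 0.8 = 166.4, about 6 below 172.

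**The dropout that the stated sizes tolerate.**
- 206: 1 − 172/206 = 34/206 = 16.5%.
- 208: 1 − 172/208 = 36/208 = 17.3%.

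**The size that would cover 20%.** 172 / 0.8 = 215, and 215 / 8 = 26.9 per class. With 27 per class, 8 × 27 = 216 and 216 × 0.8 = 172.8, which keeps 172.

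**Power at the level of the child** (same t test, no allowance for clustering):

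| Children analysed | Per arm | Power |
|---|---|---|
| 172 | 86 | 90.3% |
| 166.4 (208 less 20%) | 83.2 | 89.4% |
| 164.8 (206 less 20%) | 82.4 | 89.1% |

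Against the stated 90%, the shortfall is 0.6 to 0.9 percentage points.

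**Scale against clustering.** The 172 equals the size for individual randomisation, so it contains no design effect, although classrooms are randomised, four per arm. The article gives no intraclass correlation. As an illustration only, take an assumed 0.01 to 0.05. With 164.8 / 8 = 20.6 children analysed per class, the design effect is 1 + 19.6 × 0.01 = 1.196 up to 1 + 19.6 × 0.05 = 1.98. The 164.8 children then carry the information of about 138 down to about 83 independent ones. The dropout shortfall of 7 children is small beside that.

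**The case against.** The strongest reply is that the text fixes no dropout rate. It says that the sample is increased by 20%, and that increase is computed correctly. The rates in the cited similar studies are not visible. If they were 16.5% or less, 206 would be enough. This stands, and it makes the point conditional. It does not remove the point: the 20% is tied directly to dropout, no other rate is offered, and a reader cannot tell which loss the design is meant to withstand.

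A second reply is that 26 is a minimum and whole classes enter, so the design starts from at least 208 children, and an average class of 27 would close the gap with no change to the plan. This also stands, but the guaranteed floor still falls about 6 short at 20% loss.

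A third is that less than one point of power changes no conclusion. That is correct, and it is why the point is minor.

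Two stronger readings are tempting. A reader might infer that the trial plans for a 20% loss as a stated fact; the article states only a 20% increase. A reader might also infer a serious loss of power, for instance by assuming heavier loss at the follow-up one year after the intervention (T3). The article gives no dropout figure for T3 or any other time point, so nothing in it supports a larger effect than the one shown above.

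**Conclusion.** The point holds as a conditional and minor correction. The 206 comes from multiplying by 1.2. If 20% is the expected dropout, neither 206 nor the 208 floor keeps the 172 children stated as required; they leave about 165 and 166. The arithmetic is certain. Taking 20% as the expected loss is an inference, though the natural one. The power figures rest on a two-sided 0.05 test and d = 0.5. They are individual-level values, not the power of this classroom-randomised design. Clustering is a separate and larger matter that this correction does not address.

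**What to change.** Restate the Sample size sentence without enrolling more children:

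- Give the dropout rate expected from the similar studies.
- Say that 206 children keep 172 analysed only if dropout is at most 16.5%, or 17.3% for the minimum of 208, and that about 165 to 166 remain at 20% dropout.
- If a power figure is quoted for that case (about 89%), label it as an individual-level value that ignores classroom clustering.

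If classes are still being chosen, 172 / 0.8 = 215 is the total consistent with a 20% loss, which means 27 per class in 8 classes. Both figures hold only before any design effect and would have to be derived again once clustering is included. The article describes the study as ongoing until December 2018, so the restatement may be the only part that can still be acted on. It costs one corrected sentence and a slightly less favourable stated figure.
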